#### Inclusion criteria

- Hong Kong residents aged 18 or above
- Smoke at least 1 cigarette per day in the past 3 months
- Able to communicate in Cantonese (including reading Chinese)
- Exhaled carbon monoxide (CO) 4 ppm or above, assessed by a validated CO Smokerlyzer.
- Intent to quit / reduce smoking
- Using a cell phone with instant messaging tool (e.g. WhatsApp, WeChat)
- Able to use instant messaging tool (e.g. WhatsApp, WeChat) for communication

#### Exclusion criteria

- Smokers who have communication barrier (either physically or cognitively)
- Have participation in other smoking cessation programmes or services

### **8.2 Procedures**

#### ***Phase I: Develop a smoking cessation training curriculum for the staff from NGOs and HKU***

The smoking cessation training curriculum will be designed to illustrate the psychological and behavioral therapies in managing the care of the smokers. Throughout the training, participants will be taught a variety of topics by trained nurses and trained smoking cessation counsellors including: (1) Introduction of the Quit-to-Win Contest & the RCT; (2) Smoking trend and knowledge of health hazards from smoking; (3) COSH and social marketing on smoking cessation; (4) Recruitment strategies: How to approach smokers; (5) Experience sharing in communication with

smokers; (6) Assessment of quitting readiness and individualized brief counselling; and (7) Technical skills such as conducting surveys and use of Smokerlyzers and advice on smoking reduction. At the end of the program, participants should be capable of delivering brief advice of smoking cessation for smokers. Upon completion of the training program, a certificate of attendance will be awarded to each participant. The outcomes of the training will be evaluated through a self-administered survey before, immediate after, and 6 months post-training, which includes knowledge, attitudes, and practice of smoking cessation intervention.

### ***Phase II: Process evaluation of the recruitment activities***

#### ***Quality assurance***

Throughout the process evaluation, the trained staff from HKU and NGOs will be monitored on site. Spot checks will be conducted at every venue by an investigator or a more senior research assistant to ensure a consistent delivery of the interventions proposed. They will also be responsible to monitor the whole process of each recruitment activities, and record necessary information related to the recruitment input, outcome and other environmental factors. Recruitment input includes the number of recruitment workers, posters and leaflets used. Recruitment outcome includes the number of smokers and non-smokers approached and the number of people who pay attention to the recruitment booth. The research staff will also assess the environmental factors including weather, date, time, location, facilities that may have an impact on the achievement of the recruitment sessions.

### ***Phase III: Recruit and provide smoking reduction/cessation counselling***

At the recruitment sessions, smoking cessation counsellor will measure the potential participant's level of carbon monoxide (CO) in exhaled air, screen their eligibility for entering the contest, and provide the self-help smoking cessation booklets developed by the Hong Kong Council on Smoking and Health (COSH). Then the counsellor will explain and invite the participants to join the RCT on smoking cessation intervention. Written consent for voluntary participation in the trial will be obtained before administering the baseline questionnaire and delivery of the intervention for the participants.

#### ***Hypothesis***

The major research hypothesis is: "Cocktail" intervention of brief advice, instant messaging and active referral (AIR) group (Group A) will have higher smoking cessation rate than the control group (Group B). The other hypotheses for Group A vs.

vs. Group B that the former will have higher services use rate, validated smoking cessation rate and smoking reduction rate.

### Quit to Win Contest

In the Quit to Win study, two-arm RCT will be conducted to test the effectiveness of “cocktail” intervention of brief advice, instant messaging and active referral (AIR) SC services use in achieving smoking abstinence. A detailed flow chart of the RCT is attached (Appendix 1).

### Intervention group

Smokers in intervention groups will receive a combined “cocktail” intervention of (i) brief advice, (ii) instant messaging and (iii) active referral.

#### (i) Brief intervention using AWARD model (Group A)

Smokers will receive AWARD intervention delivered by the SC counsellors who completed the TTT programme and a brief warning leaflet emphasising on smoking harms (especially one out of two smokers will be killed by smoking, and the risk could be up to 2/3 for high risk smokers) and benefits of cessation.

#### AWARD model

AWARD will be delivered to smokers onsite and this includes: **A**sk about smoking history, **W**arn about the high risk (*with a brief health warning leaflet, see below for information*), **A**dvice to quit as soon as possible and not later than a quit date (which will qualify them for the QTW prizes), **R**efer smokers to smoking cessation services (*with a referral card, see below for information*), and **D**o it again: to repeat the intervention; participants who fail to quit or relapse will be encouraged to quit again (and those who have quit will be encouraged to prevent relapse) during each telephone follow-up. The whole process of AWARD can be delivered within 30 seconds to 1 minute.

#### a) Brief leaflet on health warning and smoking cessation

The 2-side colour printed A4 leaflet, which systematically covers the most important messages to motivate smoking cessation and being used in QTW 2015, will be disseminated to smokers during the counselling, with improvements if necessary.

b) Referral card

The 3-folded “Smoking Cessation Services” card which was developed and used since QTW Contest 2015 will be disseminated to smokers in this project, with improvements if necessary. The content consists of brief information and highlights of existing smoking cessation services, contact methods, motivation information and strong supporting messages or slogans.

**(ii) Semi-personalized instant messaging interaction**

Similar to QTW2016, regular messages will be sent via instant messaging (IM) services (e.g. WhatsApp, WeChat) since initial contact and until 3-month after baseline with a tapering schedule:

- Baseline to 4-week (1-month): 2 times/ week (8 in total)
- 4-week to 8-week (2-month): 3 times/ 2 weeks (6 in total)
- 8-week to 13-week (3-month): 1 time/week (5 in total)

SC messages will generally include benefits of SC, encouragement on abstinence and use of SC services, tips on avoiding/ handling craving and reminder of participating in telephone follow-up. An IM message will also be sent at 26-week as a reminder of 6-month follow-up, making up a total of 20 regular messages.

In addition to sending regular messages, semi-personalized instant messaging (IM) interactions (e.g. WhatsApp, WeChat) will be developed and smokers can communicate with counsellors in real-time during office hours (0930 to 1830 every working day) since initial contact and until 3-month after baseline. Our counsellors will trigger the conversation and invite the smokers to response. Semi-personalized conversation will be developed according to smokers’ basic characteristics and intention to quit and use existing SC services. Through real-time online chatting, smokers can acquire SC information immediately and gain social support. Counsellors can also keep contact with the smokers to offer help, positive encouragement, reflections and reminders about SC according to smokers’ personal needs and to encourage them to seek SC services. Details of successfully booked SC appointment (e.g. SC services address, contact information, date, appointment number etc.) will be delivered to the smokers using IM. All smokers will receive a reminder-to-attend IM messages 1-3 days before the appointment date. The details of IM

development is described below. We have extensive experience in IM and SMS designed for smokers.

(iii) Active referral to SC services

Similar to QTW Contest 2016, smokers in this project will be introduced to various SC services in Hong Kong (using the referral card) and be motivated to use the services. Interventions in this group are designed to promote using the existing SC services to increase abstinence rate. Cochrane review suggests that more intensive contact with smokers is the way to increase participation in smoking cessation programmes (Belisario, Bruggeling, Gunn, Brusamento, & Car, 2012).

Research staff will monitor the use of SC services by smokers at each follow-up (1, 2, 3 & 6-month) and assist participants to book or re-book appointments if necessary. We shall liaise with the existing service providers and seek their assistance in helping the smoker in a timely manner.

**Control Group: very brief SC advice (Group B)**

Participants in the control group will receive minimal intervention, including: (1) Placebo short-message service (SMS) reminder messages to participate in telephone follow-up (4 in total; 1 each for 1-, 2-, 3- and 6-month follow-up) ; (2) very brief, minimal and general smoking cessation advice, such as “Please quit smoking for improving health and save money”, “Please refer to the booklet for the details about smoking cessation” and “Please call us if you have any enquiry”.

Subjects in the both intervention and control group will also receive a 12-page generic self-help SC booklet provided by COSH (<https://tinyurl.com/ydy3xssu>).

Table 1. Summary of intervention in 2 groups

|                                                | Intervention
(Group A) | Control
(Group B) |
|------------------------------------------------|---------------------------|----------------------|
| Instant messaging support + regular messages   | ✓                         |                      |
| Active referral to SC service                  | ✓                         |                      |
| AWARD advice + warning leaflet + referral card | ✓                         |                      |

|                      |   |   |
|----------------------|---|---|
| Placebo SMS messages |   | ✓ |
| Very brief SC advice |   | ✓ |
| 12-pg COSH booklet   | ✓ | ✓ |

### **Non-trial Group**

Those who are unable to read or communicate using Chinese, or those who refuse to participate in the RCT, can still participate in the QTW Contest and will receive the same monetary incentive if he/she passes the biochemical validations at 3- and 6-month. This group will be analysed separately from the RCT.

### **Follow-up**

All participants in the RCT will be followed-up at 1-, 2-, 3- and 6-months by telephone interview to assess their smoking status and quitting progress.

For those unreachable participants at the schedule follow-up time, we shall make further calls, but limited to a maximum of 7 calls and 1 voice message as a reminder for their quitting. Self-reported quitters (no smoking in past 7 days) at 3- and 6-month follow-up will be invited for biochemical and non-biochemical validation. Biochemical validation includes the measurement of exhaled CO level and saliva cotinine level of the participants, which will be conducted by research assistants. The non-biochemical validation includes asking the quitter a few questions on the consequences of quitting, confirming quitter's quitting status by family members and assessment on the quitter by the interviewer. These are broadly similar to previous QTW Contests.

### ***8.3 Randomization***

By cluster randomization, all participants recruited in a particular recruitment session (one day may have more than one activity) will be allocated to one of the RCT groups. Block randomization will be used to allocate the recruitment activity into the two RCT groups to ensure the number of recruitment activities for the two RCT groups is similar. The numbers for the permutation in the blocks will be generated with the website <http://www.random.org> (a website for generating random integers), and then merge with the list of all recruitment days.

### ***8.4 Instruments***

#### ***Phase I***

*A course evaluation form and a self-administered questionnaire including knowledge, attitude, and practice of smoking cessation will be completed by the participants of the training workshops (Appendix 2).*

## ***Phase II***

A process evaluation form will be used to record the recruitment outcomes and observations including the number of people reached in the recruitment sessions of all recruitment sessions. It will be administered by the investigators or research staff.

## ***Phase III***

### ***Quit to Win***

Three sets of questionnaires will be adapted from our previous Quit to Win Contest conducted in 2015. These include: (1) a baseline questionnaire which collects demographic data, smoking behavior, quit attempts, smoking-related psychological factors and perceived social support when they participated the Contest (Appendix 8); (2) a set of follow-up questionnaires 1 month & 2 month booster interventions (Appendix 9a-b and 10a-b); and (3) a set of follow-up questionnaires for 3- & 6-months (Appendix 11a-b and 12a-b) which collects information on smoking behavior, quit attempts, smoking-related psychological factors and perceived social support in the quitting process, as well as the impact of the Quit to Win Contest. An interview guide will be developed for qualitative interviews with quitters and non-quitters.

## ***8.5 Sample size***

### ***Phase I***

All staff/helpers from the participated NGOs and HKU who participate in the recruitment will be invited to attend the training program. A total of 100 participants (including a minimum of 36 NGO staff and HKU student helpers) can join the smoking cessation training program.

### ***Phase II***

COSH targeted to organize at least 2 recruitment sessions in each of the 18 districts in Hong Kong. There will be about 70 recruitment sessions to be evaluated.

### ***Phase III***

#### ***Quit to Win***

The sample size calculation is based on the primary outcome of biochemically validated 7-day point prevalence quit rate at the 6-month follow-up. Result from QTW2015 showed that the intention-to-treat biochemically validated abstinence at 6-month was 5.1%. Based on a meta-analysis of mobile health intervention for smoking

cessation, the intervention effect on validated quit rate at 6-month has an RR of 1.83 (Whittaker, McRobbie, Bullen, Rodgers, & Gu, 2016). To detect a significant difference of quit rate between Group A and Group B with a power of 80% and 5% significant level, we will need 586 subjects per group. The design effect is estimated to be negligible, based on the results from QTW2010 which shows an intra-cluster correlation of <0.001 for biochemically validated abstinence at 6-month (Chan et al. 2017). Total sample size needed =  $586 \times 2 = 1,172$ .

For the post-intervention qualitative study, a purposive sample of quitter and non-quitter will be interviewed with sample size determined by data saturation.

### 8.6 Statistical Analysis

Data will be entered into SPSS for Windows (version 23). A logic check program will be installed for entry validation. Descriptive statistics such as frequency, percentage, and mean will be used to summarize the outcomes and other variables. Chi-square tests and t-tests will be used to compare outcome variables between subgroups. Generalized Estimating Equation (GEE) models will be applied to test the intervention effect, to identify the baseline predictors of successful quitting and to assess the changes in smoking-related factors over time. The intention-to-treat (ITT) analysis will be used such that those lost to contact and refused cases at the follow-ups will be treated as a failure to achieve any cessation outcome. Complete case analysis will also be conducted after excluding participants with missing data.

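### Sessions are randomised, but section 8.6 names chi-square and t-tests for outcomes without allowing for clustering, GEE is not tied to the randomised unit, and section 8.3 states that unit two ways

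*Protocol*

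**What the plan says.** **Unit of randomisation.** The protocol describes a two-arm cluster RCT (section 8, and section 8.1 under Phase III). Section 8.3 gives one allocation to "all participants recruited in a particular recruitment session (one day may have more than one activity"), and blocks the sequence so that the arms have similar numbers of activities. It then says that the numbers are generated "and then merge with the list of all recruitment days".

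**Analysis.** Section 8.6 states: "Chi-square tests and t-tests will be used to compare outcome variables between subgroups". The next sentence names GEE for three tasks: testing the intervention effect, and then "to identify the baseline predictors of successful quitting and to assess the changes in smoking-related factors over time". The section names no clustering unit and makes no other adjustment for the session.

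**Design effect.** Section 8.5 (Quit to Win) calls the design effect negligible, citing an ICC below 0.001 from the 2010 contest. That ICC is for biochemically validated abstinence at 6 months, the primary outcome. Section 5(c) lists self-reported 7-day abstinence, service use and smoking reduction among the secondary outcomes, and the protocol gives no ICC for these.

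**The concern.** Ordinary chi-square and t-tests assume independent individuals. Here everyone recruited in a session is in the same arm, so any positive within-session correlation adds to the variance of the arm difference, and these tests leave that part out. P-values then tend to be too small and intervals too narrow.

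GEE removes the problem only if its clusters are the randomised units. For change over time the natural cluster is the participant, followed at 1, 2, 3 and 6 months. A GEE clustered on the participant alone would still ignore the session. Because one sentence covers both uses, the text does not settle which unit is meant.

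The session/day wording matters for the same reason. If two activities fall on one day, a list of days does not show whether they share one allocation or get two. The analysis must cluster on whatever was actually allocated. If that is the day, there are fewer and larger clusters than 70 sessions imply.

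**Working it through.** **1. The plan's own figure.** Inputs from section 8.5:
- Control rate: "the intention-to-treat biochemically validated abstinence at 6-month was 5.1" per cent.
- Effect: "the intervention effect on validated quit rate at 6-month has an RR of 1.83", so the Group A rate is 0.051 × 1.83 = 0.09333.
- Error rates: "with a power of 80% and 5% significant level" (sidedness not stated; two-sided reproduces the figure).

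Pooled-variance formula, no continuity correction, with mean rate (0.051 + 0.09333)/2 = 0.07217 and difference 0.04233:

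n = [1.960 × √(2 × 0.07217 × 0.92783) + 0.842 × √(0.051 × 0.949 + 0.09333 × 0.90667)]² / 0.04233² = 585.4, rounded up to 586.

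This matches "we will need 586 subjects per group" exactly, with no design effect applied.

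**2. Cluster size.** Section 8.5 (Phase II) expects about 70 sessions, so m = 1,172/70 = 16.74. The same section's minimum of 2 sessions in each of 18 districts gives 36 sessions and m = 1,172/36 = 32.56.

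**3. True size of an unadjusted two-sided 5% between-arm test.**
- Design effect, equal sessions: DE = 1 + (m − 1) × ICC.
- Design effect, unequal sessions: DE = 1 + ((1 + CV²) × m − 1) × ICC.
- True size = 2 × (1 − Φ(1.96/√DE)).

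With 70 sessions:

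| ICC | Source | DE, equal | True size | DE, CV 0.6 (assumed) | True size |
|---|---|---|---|---|---|
| 0.001 | upper bound in section 8.5, primary outcome | 1.016 | 5.2% | 1.022 | 5.25% |
| 0.01 | assumed | 1.157 | 6.8% | 1.218 | 7.6% |
| 0.02 | assumed | 1.315 | 8.7% | 1.435 | 10.2% |
| 0.03 | assumed | 1.472 | 10.6% | 1.653 | 12.7% |

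With 36 equal sessions, ICC 0.001 gives DE 1.032 and true size 5.4%; an assumed ICC of 0.01 gives DE 1.316 and 8.8%.

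**4. Sample size.** At ICC 0.001 with 70 sessions, 586 × 1.016 rounds up to 596 per group, or 1,192 in total. That is inside the recruitment target of 1,200 in section 8.1 (Phase II). Power at 586 per group is 79.4%.

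**5. The unit.** Section 8.1 (Phase III) and the opening of section 8.3 allocate by session or activity. The parenthesis in 8.3 says that a day may hold more than one activity, so the two units differ. The last step of 8.3 uses days. The number of recruitment days is not given, so the effect of using the day cannot be computed.

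**The case against.** Section 8.6 gives the two methods different jobs. GEE, which suits clustered data, is named for the intervention effect. The chi-square and t-tests are for subgroups, a word that the protocol uses nowhere else; it calls the arms groups. This stands. A reader might infer that the primary comparison will rest on an unadjusted chi-square test, and the text does not say so. The sentence allows unadjusted between-arm outcome comparisons but does not fix them. The sizes in the table apply only if the tests are used between arms.

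The clustering variable, working correlation and variance estimator are commonly left to an SAP, which is not shown. The primary outcome is a single 6-month time point, so clustering on the participant would serve no purpose there. The protocol also commits to CONSORT and discusses the ICC. This too stands: the unnamed GEE cluster alone is missing detail, not an error. What remains is that the section pairs it with tests that assume independence, and that the unit to cluster on is itself unclear.

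Only one ICC is documented, and it makes the effect trivial. That is right for the primary outcome. It is tempting to add that the secondary outcomes must cluster more because they depend on a session's counsellors and venue, but the protocol does not show this. On-site advice comes from that session's staff, while three months of messaging, booking help and telephone follow-up come later and are not described as session-specific. The secondary ICCs are unknown.

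The reference to days may be loose wording for the recruitment schedule. That is possible, but the sentence governs how allocation is carried out, and an SAP could not settle it afterwards.

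**Conclusion.** The point holds in a limited form. Section 8.6 names tests that assume independence for outcome comparisons in a cluster-randomised trial, with no clustering allowance, and does not tie GEE to the randomised unit. Section 8.3 gives that unit as session or activity in one place and as day in another.

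For validated abstinence at 6 months the consequence is negligible at the protocol's own ICC: true size at most about 5.2% with 70 equal sessions. The documents do not support a claim that the primary result would be materially distorted or that the trial is too small.

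The possible exposure is in the secondary outcomes, if they are compared between arms without adjustment. A true size of 6.8% to 10.6% rests on assumed ICCs of 0.01 to 0.03, and 7.6% to 12.7% also on an assumed CV of 0.6. These figures show a range and do not predict the trial's error rate. The change is worth making because it costs almost nothing.

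**What to change.** - **Section 8.3:** state one randomised unit, session or day, and merge the random sequence with the list of that unit.
- **Section 8.6:** base all between-arm outcome inference on GEE clustered on that unit with robust standard errors. Do the same in models with several time points, where robust variance at that level also covers repeated measures on a participant, who belongs to one unit only.
- **Section 8.6:** keep chi-square and t-tests for descriptive use, not for between-arm outcome p-values. Reserving them for the Phase I training data would not help, because those are repeated measurements on the same trainees.
- **Data:** record the unit's identifier in each participant's record. The protocol describes activity-level process records but does not say that participant data carry this identifier.

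The cost is a few sentences, one data field and slightly wider intervals. The sample size does not change.
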